#### Maternal Depressive Symptoms

The curriculum addressing maternal depressive symptoms is adapted from the *Mothers and Babies Course*, a manualized group treatment program for postnatal depression [29,30]. The *Mothers and Babies Course* is an evidence-based program that has been demonstrated to reduce maternal depressive symptoms in efficacy trials [29,30]. Our adaptation of the *Mothers and Babies Course* makes it appropriate for delivery in combination with the parenting intervention content. The program is based on the cognitive behavioral theory and attachment theory and targets the unique needs and stressors mothers face during the postnatal period. It has achieved promising results in initial trials delivered alone and in combination with a home-visiting program provided to low-income mothers. In the app, module content is presented in the form of text and video or audio messages. Each module provides mothers with a task to complete (eg, behavioral activation), with the aim of prompting group discussion and problem solving around the task, and engaging mothers in managing mood and the stressors of parenthood. The timing of the presentation of depression modules is based on children’s ages, and they are largely “self-help” rather than requiring nurse assistance for their completion. The primary role of nurses is to encourage the use of the modules. Nurses receive training in the use of their content from a clinical psychologist trained in the delivery of the *Mothers and Babies Course*.

#### Mental Health First Aid

All nurses delivering the intervention completed the *Mental Health First Aid* [31,32] training program with the aim of improving their ability to identify depressive symptoms and provide support for mothers experiencing symptoms of postnatal depression. This training program was designed to help lay individuals and professionals develop skills in working with individuals developing mental health problems or in a mental health crisis. A meta-analysis of trials evaluating *Mental Health First Aid* has shown that this training increases participants’ knowledge regarding mental health, decreases their negative attitudes, and increases supportive behaviors for individuals with mental health problems [33].

The use of these curriculum and training components ensured that the intervention appropriately addressed both maternal depressive symptoms and problems with parenting.

### Standard Care

Only mothers in the intervention arm had access to the internet intervention. However, mothers in both intervention and comparison groups had access to standard care arrangements.

For the vast majority of mothers, standard care comprised a single home visit by a CaFHS nurse who checks the health of mothers and infants, provides advice about issues relevant to infant care, and offers information about other relevant community services available for mothers and infants.

### Outcome Measures

All measures were completed when infants were aged 1-2 (preintervention), 8, and 12 months. Measures were completed during home visits conducted by trained field workers to ensure high-quality data. The primary outcomes for the trial were the level of maternal depressive symptoms and observed the quality of maternal caregiving assessed when infants were aged 8 and 12 months.

#### Maternal Depressive Symptoms

The EPDS is a 10-item self-report questionnaire that assesses the level of depressive symptoms experienced by mothers during the postnatal period [22]. Questions assess symptomatology during the previous 7 days and utilize a 4-point response scale and include items such as *“I have blamed myself unnecessarily when things went wrong* ” and “*Things have been getting on top of me*.” Scores on all items are summed and recommended cutoff points are available to identify mothers who would benefit from additional support [34]. Scores range from 0 to 30, with higher scores indicating higher levels of depression symptoms.

#### Maternal Caregiving

##### The Parenting Sense of Competence Scale

PSCS is a 16-item self-report questionnaire designed to measure the parental efficacy and satisfaction in the parenting role. Items are rated on a 6-point response scale and include “*Being a parent is manageable, and any problems are easily solved* ” and “*Being a parent makes me tense and anxious*.” Scores range from 16 to 96, with higher scores indicating higher levels of parenting competence. The scale has been successfully used with Australian mothers and has satisfactory psychometric properties [23,24].

##### Nursing Child Assessment Satellite Training Scales

NCAST scales are designed to assess the quality of mother–child interactions, including the sensitivity to cues, response to distress, fostering social–emotional functioning, and fostering cognitive growth [26]. For the purpose of this study, we used the Teaching Scale suitable for use with 0-36-month olds. The scale utilizes 3-5-minute video-recordings of mothers teaching their child a skill appropriate to the age of their child, selected from a list in the NCAST training manual. Field workers recorded mothers completing the teaching interaction during home visits. Subsequently, research assistants who have completed the NCAST training program coded the video-recordings to generate a total score and subscale scores [26]. Items were coded as “Yes” or “No” and include “*Child attempts to engage caregiver in eye-to-eye contact* ” and “*Caregiver praises child’s successes or partial successes*.” Scores range from 0 to 73, with higher scores indicating higher levels of positive mother–child interaction quality. The NCAST scale has been found to have satisfactory psychometric properties [26].

##### Parenting Stress Index

PSI is a widely used self-report questionnaire designed to assess parent and child characteristics relevant to “parent-child systems” with acceptable psychometric properties [25]. Items consist of statements such as “*I often have doubts about my ability to handle being a parent* ” and “*I expected to have closer and warmer feelings for my child than I do and this bothers me* ” and are rated on a 5-point response scale. Relevant subscales assess maternal perceptions of parenting competence, the quality of parent-child relationships, and the impact of parenting responsibilities on autonomy and self-identity. Higher scores indicate worse functioning with scores for parenting competence (11 items, excluding 2 items assessing parental education) and the quality of parent-child relationships (7 items) with range 11-55 and 7-35, respectively.

#### Other Measures

##### Service Utilization

Service utilization was included as a secondary outcome for this study, as it is possible that mothers who received eMums plus required less support from other services. This information is routinely recorded by CaFHS, including the number of clinic visits and the number of health checks. Maternal self-report questionnaires identified other services (eg, general practitioners) used by mothers and infants.

##### Intervention Quality

Mothers’ perceptions about the quality of the support provided by the intervention were assessed using a 40-item questionnaire after 8 months, which we have developed for this purpose. Items asked about the intervention effectiveness and usability of the mobile phone app. After 12 months, mothers were asked to answer 10 questions about what had been the most useful elements of the intervention.

##### App Usage

The extent to which mothers used the app was recorded. Data were automatically collected on a number of indices, including the number of log-ins, comments, and replies that mothers post, as well as the amount of time spent in different sections of the app.

### Analysis Plan

Analyses will be by intention-to-treat and focus on intervention effects on maternal depression (EPDS) [22], mother–child interactions (NCAST) [26], and maternal caregiving competence (PSI and PSCS) [23,25] at 8 and 12 months. General linear modeling techniques will be used when the scores are continuous outcomes, including log-binomial regression for dichotomous outcomes (eg, the percentage of mothers scoring above recommended EPDS cutoff scores). Data collected at baseline will be used to control for any imbalances between the trial arms. Multiple imputations will be used to address missing data where this approach is appropriate.

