**Figure 1 figure1:**
[figure not shown]
Flow chart of participants. EPDS: Edinburgh Postnatal Depression Scale; N/A: not available.

Following randomization, mothers in the intervention arm were assigned to a group over the Web supported by a CaFHS nurse comprising approximately 20 mothers of similar-aged infants; they were also able to access standard care services as required. The intervention was delivered when infants were aged 2-6 months because this is (1) a key developmental period for infants; (2) a time when mothers are most vulnerable to depressive symptoms; and (3) as previously shown, it is the time when mothers most actively seek information from nurses and want to share and exchange ideas with each other [18].

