### Randomization

The trial used group randomization with blocks of 20 eligible mothers consecutively identified and then randomized to either the intervention or comparison arms of the study. A group randomization sequence was used to determine the arm to which each group was assigned. This approach ensured that mothers’ groups in the intervention arm contained no more than 20 mothers per group. The randomization schedule was generated by a statistician who was independent of the study team. The research team was blind to group allocation at the time of recruitment and assignment of mothers to the study groups. However, due to the nature of the intervention, after the intervention commenced, it was not possible to keep research staff or field workers blind to the groups to which mothers had been allocated. The exception to this was research staff members coding the NCAST Parent-Child Interaction scale, who were blind to the group allocation while completing coding.

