### Sample Size

The sample size target for this study was 160 (80 in each trial arm). This sample size would provide 0.80 power to detect an effect size of Cohen *d*=0.4 at an alpha of .05.

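### Whole groups of up to 20 mothers are randomised, but the named models and the sample size take no account of the group; if outcomes correlate within groups, type I error exceeds the nominal 5%

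*Protocol article*

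**What the plan says.** The Randomization section of the protocol article sets the unit: "The trial used group randomization with blocks of 20 eligible mothers consecutively identified and then randomized to either the intervention or comparison arms". It continues: "A group randomization sequence was used to determine the arm to which each group was assigned". The purpose given is group size: "This approach ensured that mothers’ groups in the intervention arm contained no more than 20 mothers per group".

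Participants and Recruitment (after Figure 1) adds that intervention mothers were "assigned to a group over the Web supported by a CaFHS nurse comprising approximately 20 mothers of similar-aged infants". Intervention Delivery describes a chat room whose posts every group member can see, with extra content posted by the nurse to suit her group. Under Maternal Parenting Problems, nurses are said to tailor the curriculum group by group.

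The Analysis Plan is intention-to-treat and reads: "General linear modeling techniques will be used when the scores are continuous outcomes, including log-binomial regression for dichotomous outcomes". It adds baseline adjustment for imbalance between arms, and multiple imputation. Sample Size gives a target of 160 mothers, 80 per arm, and says: "This sample size would provide 0.80 power to detect an effect size of Cohen *d*=0.4 at an alpha of .05". The article nowhere mentions clustering, an ICC, a design effect, a random effect or a robust variance.

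**The concern.** One allocation is made per group, so the comparison between arms rests on about 8 randomised units, about 4 per arm. A general linear model or log-binomial regression fitted to individual mothers, with no term for the group, takes its error variance from differences between mothers and works with about 158 residual degrees of freedom. The group allocation supports about 6.

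There are plausible routes to correlation within groups. In the intervention arm these are the shared nurse support, the chat room and the tailored content. In both arms, a group is a run of consecutively identified mothers and so shares a recruitment window. If correlation exists, the model's standard errors are too small and its confidence intervals too narrow. A good or bad group could then be read as an effect of the intervention. This bears on the primary outcomes, and the article presents the trial as a basis for adoption by the service.

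**Working it through.** **Inputs.** From Sample Size: 160 mothers, 80 per arm, d = 0.4 (SD = 1), alpha 0.05, power 0.80; sidedness is not stated. From Randomization and Participants and Recruitment: groups of about 20, at most 20. The ICC is not given, so 0.01 to 0.10 is assumed. The number of groups is not stated; 160/20 = 8, or 4 per arm, is used.

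**Step 1: the plan's own power figure.** For independent mothers and no covariates, power = Φ(d·√(n/2) − z), with d·√(n/2) = 0.4·√40 = 2.530.
- Two-sided: Φ(2.530 − 1.960) = Φ(0.570) = 71.6%. Reaching 80% would take 99 per arm.
- One-sided: Φ(2.530 − 1.645) = Φ(0.885) = 81.2%.

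The stated 0.80 is thus reproduced per mother with a one-sided test. A two-sided test would reach it only with a gain from baseline adjustment (a baseline correlation of about 0.43), which the article does not mention. Neither calculation includes any inflation for groups.

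**Step 2: type I error of a model without the group.**
- Design effect: DE = 1 + (20 − 1)·ICC.
- Both arms correlated: true variance / model variance = DE.
- Intervention groups only: the ratio is the average over the two arms, (DE + 1)/2.
- Actual two-sided type I error = 2·(1 − Φ(1.96/√ratio)).

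| ICC | DE | Ratio, intervention only | Type I error, intervention only | True SE / model SE, both arms | Type I error, both arms |
|---|---|---|---|---|---|
| 0 | 1.00 | 1.000 | 5.0% | 1.00 | 5.0% |
| 0.01 | 1.19 | 1.095 | 6.1% | 1.09 | 7.2% |
| 0.02 | 1.38 | 1.190 | 7.2% | 1.17 | 9.5% |
| 0.05 | 1.95 | 1.475 | 10.7% | 1.40 | 16% |
| 0.10 | 2.90 | 1.950 | 16% | 1.70 | 25% |

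Simulation of 8 groups of 20 (40,000 runs per ICC) agrees. For ICC 0.01, 0.02, 0.05 and 0.10 it gave 5.9%, 7.2%, 10.6% and 16.3% with correlation in intervention groups only, and 7.0%, 9.9%, 16.0% and 25.5% with correlation in both arms.

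**Step 3: power when the group is respected.** A two-sided t-test on group means has 8 − 2 = 6 df and noncentrality 0.4/√(2·DE/80), taking the same ICC in both arms. Power for d = 0.4 is 56% at ICC 0, 49% at 0.01, 44% at 0.02, 33% at 0.05 and 24% at 0.10. In the same simulation its type I error stayed near 5%.

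**The case against.** The Analysis Plan is four sentences in a journal article. It speaks loosely of modelling techniques, writes out no model, and never says that mothers are treated as independent. Either named model could be fitted with a group term, and an unseen analysis plan may add one. It is true that independence is inferred here and not stated. The point still stands as a mismatch: the article commits to a model class and to a sample size, it puts the group in neither, and it describes a design in which the group is the unit allocated.

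Three stronger readings are tempting, and the documents do not support them.
- *That type I error is certainly above 5%.* This needs ICC > 0, and no ICC is given. At ICC 0 the test holds its level. Nothing in the article supports the upper end of the range at 12 months, about six months after the groups ended, and baseline adjustment could lower the residual correlation.
- *That the both-arms figures are the natural ones.* The shared nurse support and chat room exist only in the intervention arm. Comparison mothers are linked, as far as the text shows, only by when they were recruited. The intervention-only row fits the described mechanism better.
- *That the sections contradict each other on the unit of randomisation.* Participants and Recruitment speaks of randomising mothers, and after Figure 1 says "Following randomization, mothers in the intervention arm were assigned to a group over the Web supported by a CaFHS nurse". Both can be shorthand for allocating a block and then placing its mothers in an online group. This calls for clearer wording; it is not a proven conflict.

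Nor does the article say that every group had a different nurse. The count of 8 is derived from a maximum group size, so actual groups could be smaller and more numerous.

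**Conclusion.** The concern holds in conditional form. The plan as written leaves out the unit of randomisation, and a model without it is too liberal whenever outcomes correlate within groups. The excess is modest at small ICCs: about 6% to 7% for ICC 0.01 to 0.02 with correlation in intervention groups only. It is large at the upper end of the assumed range: 16% (intervention only) to 25% (both arms) at ICC 0.10. If the randomisation were read as individual, the intervention-only figures would still apply, because intervention mothers are nested in nurse-supported groups. Confidence is high on the mismatch and on the direction of the error when ICC > 0. The size rests on an assumed ICC and on 4 groups of 20 per arm.

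**What to change.** **Analysis Plan.** Analyse by the groups randomised.
- Continuous scores: pre-specify one primary method, for example a linear mixed model with a random intercept for randomisation group and Kenward-Roger or Satterthwaite degrees of freedom. Use a t-test on covariate-adjusted group means as the sensitivity analysis.
- Dichotomous outcomes: use a matching group-level or mixed-model analysis.
- Include the group in the imputation model and report the ICC.
- Do not use an uncorrected sandwich variance with so few groups.

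**Participants and Recruitment.** State that the group is the unit of randomisation, as the Randomization section does.

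**Sample Size.** State that the 0.80 power makes no allowance for group randomisation.

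**Cost.** No new data are needed, because group membership follows from the allocation. Intervals become wider and power is lower, as step 3 of the working shows: about 56% for d = 0.4 at ICC 0, 44% at ICC 0.02 and 33% at ICC 0.05 with the 6-df group-level test. Follow-up is complete, so groups cannot be added, and the report should state this loss openly.

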### Participants and Recruitment

We aimed to enroll 160 mothers of infants aged 2-8 weeks at the time that they completed their 1-4-week postnatal health check with CaFHS (Figure 1). At the time CaFHS administration staff routinely made contact with mothers to organize their postnatal health check, potential participants were asked whether they were willing to consider participating in the research project should they prove to be eligible for the study. Mothers who indicated that they were willing to consider participation were asked to consent to allow their phone contact details to be passed on to the research team, if they were eligible for the study. During the postnatal health check, these mothers completed a questionnaire comprising a 4-item parenting problems scale and the EPDS [22]. Mothers who scored >7 on the EPDS and reported, at least, 1 problem on the 4-item parenting problems questionnaire were eligible to participate. Following their postnatal health check, eligible mothers were contacted by telephone by the research team. The research team explained the study to the mother, sought verbal consent for a home visit by a member of the study’s field-worker team, and randomized mothers to either the intervention arm or the comparison (“standard care”) arm of the study. Field workers contacted mothers who had given their consent and arranged a time to visit them to complete the “formal” consent process and, where written consent was given, complete the baseline research assessment.

The exclusion criteria included mothers (1) with an EPDS score >13 and who were judged by their screening nurse to have a level of depressive symptoms that precluded their participation in the study; (2) those judged by their screening nurse to be experiencing domestic violence, illicit drug use, or other major distress that precluded their participation in the study; or (3) those who lacked sufficient English skills to complete the self-report questionnaires. Mothers with an EPDS score >13 whose nurses judged they would be able to participate in the trial were included provided they also had access to support from a family doctor or other health professional. All mothers identified as experiencing high levels of depressive symptoms (ie, >13 on the EPDS) were referred to other services, most frequently general practitioners. Such referrals occurred in both the intervention and comparison groups in this study.

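### The plan ties baseline adjustment to imbalance between arms instead of committing to adjust each outcome for its own preintervention score

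*Protocol article*

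**What the plan says.** The Analysis Plan says of continuous scores: "General linear modeling techniques will be used when the scores are continuous outcomes". It names no covariates. Its only sentence on baseline data is: "Data collected at baseline will be used to control for any imbalances between the trial arms". It does not define an imbalance, and no other section commits to a baseline covariate.

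The data for such a covariate exist. Outcome Measures states: "All measures were completed when infants were aged 1-2 (preintervention), 8, and 12 months". EPDS, PSCS, NCAST and PSI therefore each have a preintervention score.

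Three other statements bear on the point:

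- Sample Size sets 80 mothers per arm and claims: "This sample size would provide 0.80 power to detect an effect size of Cohen *d*=0.4 at an alpha of .05". It mentions no baseline correlation.
- Randomization says: "The trial used group randomization with blocks of 20 eligible mothers consecutively identified and then randomized". At the target of 160 this is 160/20 = 8 groups, or about 4 per arm.
- Participants and Recruitment places randomisation at the telephone contact. The later home visit is where mothers would, "where written consent was given, complete the baseline research assessment". The baseline scores are thus preintervention but, in the order described, come after randomisation. The eligibility screen is earlier: "Mothers who scored >7 on the EPDS and reported, at least, 1 problem on the 4-item parenting problems questionnaire were eligible to participate".

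**The concern.** A baseline score is worth adjusting for because it predicts the outcome, whether or not the arms happen to differ on it. A rationale based on imbalance puts this the wrong way round. If it is followed as written, someone must first compare the arms and then decide what enters the model. Two things are at stake.

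- **Discretion.** With no definition of imbalance, the covariate set can differ between outcomes and be settled after the data are seen. The article reports that follow-up was complete and analysis had begun, and that research staff other than the NCAST coders could not be kept blind once the intervention started. With about 8 randomised units, chance differences between arms are more likely than with 160 individually randomised mothers, so the question of what counts as an imbalance is likely to arise.
- **Precision.** If an outcome's baseline looks balanced and is left out for that reason, the variance it would have explained stays in the error term.

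**Working it through.** **Inputs from the article:** 80 per arm, d=0.4, alpha .05, stated power 0.80. **Assumptions:** alpha is two-sided (sidedness is not stated), mothers are independent, and the baseline-outcome correlation r lies between 0.3 and 0.6 (no value is given).

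**1. The plan's own figure.** In the normal approximation, power = Φ(d·√(n/2) − z), and d·√(n/2) = 0.4 × √40 = 2.530.

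- Two-sided: Φ(2.530 − 1.960) = Φ(0.570) = 0.716 (noncentral t: 0.710). Reaching 0.80 needs 2 × (1.960 + 0.842)² / 0.4² = 98.1, so 99 per arm.
- One-sided: Φ(2.530 − 1.645) = Φ(0.885) = 0.812 (noncentral t: 0.809).

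The stated 0.80 reproduces one-sided and unadjusted, but not two-sided and unadjusted. Sidedness is a separate matter. The comparisons below are all two-sided.

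**2. Always adjusting.** The residual SD becomes √(1 − r²), so the standardised effect becomes d/√(1 − r²).

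| r (assumed) | 0.4/√(1 − r²) | Power, normal | Power, noncentral t | n per arm for 0.80 (normal) |
|---|---|---|---|---|
| 0 (unadjusted) | 0.400 | 0.716 | 0.710 | 99 |
| 0.3 | 0.419 | 0.756 | 0.750 | 90 |
| 0.4 | 0.436 | 0.788 | 0.783 | 83 |
| 0.5 | 0.462 | 0.832 | 0.827 | 74 |
| 0.6 | 0.500 | 0.885 | 0.882 | 63 |

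Residual variance falls by r²: 9% at r=0.3, 25% at 0.5 and 36% at 0.6. Two-sided power of 0.80 with 80 per arm needs r of about 0.43 (normal) to 0.45 (noncentral t).

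**3. Adjusting only on imbalance.** The article states no trigger, so several were simulated (r=0.5, d=0.4, 80 independent mothers per arm, 40,000 runs; the baseline difference is in SD units).

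| Rule | Power |
|---|---|
| Never adjust | 0.71 |
| Adjust if baseline p<.05 | 0.722 |
| Adjust if difference >0.2 SD | 0.746 |
| Adjust if difference >0.1 SD | 0.781 |
| Adjust if difference >0.05 SD | 0.805 |
| Always adjust | 0.827 |

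The loss against always adjusting runs from 0.827 − 0.722 = 0.105 for the strictest trigger to 0.827 − 0.805 = 0.022 for the loosest.

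**4. Type I error.** Under the null, the p<.05 trigger rejected at 0.044 to 0.047 (r=0.5) and 0.039 (r=0.6). A null run of the three looser triggers also stayed below .05. The rule is somewhat conservative and not inflated.

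**5. What is left out.** Steps 1 to 4 treat mothers as independent. With groups of 20 the design effect is 1 + 19 × ICC. At an assumed ICC of 0.02 it is 1.38, and unadjusted two-sided power drops from 0.716 to 0.577. At 0.01 and 0.05 it is 0.640 and 0.441. The table values therefore serve to compare the rules and do not forecast the trial's power.

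**The case against.** The strongest reply is that the sentence contains no word restricting baseline data to this use, no test, no threshold and no order of looking before choosing. Putting the baseline score in every model is an ordinary way to control for any imbalance. A condensed article may also leave its covariate list to an analysis plan that is not shown. This stands in part. A reader might infer that the trial has fixed a rule under which balanced baselines go unadjusted, but the text does not establish that. The unnamed covariates are not the point either. What remains is that the article states a reason for adjusting, that the reason is imbalance, and that an analysis plan written to follow it would inherit the weakness.

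A second reply is that the loss depends on an invented trigger. That is right. A reader might conclude that power falls almost to the unadjusted level, but this holds only for a significance-test trigger. The closer the trigger comes to the literal word used, the smaller the loss.

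Third, r is assumed. The EPDS entry cut-off restricts the range, and the NCAST baseline is taken at 1-2 months; both could lower r. At r=0.3 the most that can be lost is 0.750 − 0.710 = 0.04. This stands, and it is why a range is shown.

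Fourth, a reader might suspect a false-positive problem. The null simulations show none from the trigger itself.

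**Conclusion.** The point holds as a weakness in a stated rule, and it should be corrected. The article links baseline adjustment to imbalance and does not commit to adjusting each outcome for its own preintervention score, although those scores were collected. The consequences are open covariate choice and possible loss of precision.

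Under the assumptions listed, the gain from always adjusting over never adjusting is about 0.04 in power at r=0.3, 0.12 at r=0.5 and 0.17 at r=0.6. What the current wording would forfeit is some part of that, from little to nearly all, depending on how imbalance is defined. If routine adjustment was intended throughout, nothing is lost and only the wording needs to change. The documents do not support saying that the plan forbids adjustment when arms look balanced, or that type I error is inflated.

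**What to change.** Replace the sentence on baseline data with:

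> Each continuous outcome model includes the preintervention score of that outcome as a covariate, whatever the observed balance; any other covariates are named in advance and none is chosen by observed imbalance.

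Because the baseline visit follows the randomisation call, add a sensitivity analysis for the EPDS outcome that uses the pre-randomisation screening EPDS, if the research team holds that score. The article does not show that it does: the only transfer to the team for which it describes consent is of telephone contact details. The screening score is also range-restricted by the entry cut-off, so it suits a sensitivity analysis better than the main model.

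Baseline adjustment does not replace accounting for the randomised groups, and the covariate should be fitted within whatever model does that. As analysis had already begun when the article was written, record when the covariates were fixed.

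The cost is one sentence and one secondary model. The main change needs no new data, and missing baseline scores can go into the multiple imputation already planned.
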